# Effectiveness of the MULTIPAP Plus intervention in youngest-old patients with multimorbidity and polypharmacy aimed at improving prescribing practices in primary care: study protocol of a cluster randomized trial

**DOI:** 10.1186/s13063-022-06293-x

**Published:** 2022-06-09

**Keywords:** Multimorbidity, Patient-centred care, Polypharmacy, Medication reconciliation, Decision-making, Computer-assisted, Primary health care, Cluster randomized controlled trial

## Abstract

**Background:**

The progressive ageing of the population is leading to an increase in multimorbidity and polypharmacy, which in turn may increase the risk of hospitalization and mortality. The enhancement of care with information and communications technology (ICT) can facilitate the use of prescription evaluation tools and support system for decision-making (DSS) with the potential of optimizing the healthcare delivery process.

**Objective:**

To assess the effectiveness and cost-effectiveness of the complex intervention MULTIPAP Plus, compared to usual care, in improving prescriptions for young-old patients (65-74 years old) with multimorbidity and polypharmacy in primary care.

**Methods/design:**

This is a pragmatic cluster-randomized clinical trial with a follow-up of 18 months in health centres of the Spanish National Health System. Unit of randomization: family physician. Unit of analysis: patient.

**Population:**

Patients aged 65–74 years with multimorbidity (≥ 3 chronic diseases) and polypharmacy (≥ 5 drugs) during the previous 3 months were included.

**Sample size:**

*n* = 1148 patients (574 per study arm).

**Intervention:**

Complex intervention based on the ARIADNE principles with three components: (1) family physician (FP) training, (2) FP-patient interview, and (3) decision-making support system.

**Outcomes:**

The primary outcome is a composite endpoint of hospital admission or death during the observation period measured as a binary outcome, and the secondary outcomes are number of hospital admission, all-cause mortality, use of health services, quality of life (EQ-5D-5L), functionality (WHODAS), falls, hip fractures, prescriptions and adherence to treatment. Clinical and sociodemographic factors will be explanatory variables.

**Statistical analysis:**

The main result is the difference in percentages in the final composite endpoint variable at 18 months, with its corresponding 95% CI. Adjustments by the main confounding and prognostic factors will be performed through a multilevel analysis. All analyses will be carried out in accordance to the intention-to-treat principle.

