#### Intervention group

Several key elements of the intervention must be highlighted:
Clinical data will be reviewed and registered by FPs in the electronic case report forms (eCRF) after recruitment in baseline visit.Because of the natural separation between actual electronic health records and electronic case report forms developed for the research project, final tool has been integrated into a dedicated eCRF system using a webservice WS4 version 1.2 of the CheckTheMeds® tool with the specific inputs reviewed by the FPs. This avoids barriers for FPs and the need for reintroducing double information to a separate system. Simple and detailed review of treatment plans has been incorporated. Simple review webservice outputs have been agreed after a Delphi technique with relevant stakeholders (primary care pharmacist, hospital pharmacist, family physicians, and researchers).The web-based, user-initiated DSS provide FPs with drug-therapy information that is relevant to participating patients with polypharmacy on demand. After verifying the clinical data included in the eCRF (multimorbidity and polypharmacy corrected for patient-specific factors such as sex, renal function, age and frailty), this DSS provides health professionals with clinical scenarios to optimize treatment plans for patients, the number of STOPP/START and Beers criteria, drug interactions classified based on their potential severity (traffic light system), and adjustment of the medications to other relevant clinical variables.FPs will be able to add and modify patient data in eCRF and able to review again treatment plans as many times as needed with up-to-date relevant information (new drugs, new diagnoses, change if laboratory findings about kidney function, etc.).A specific training tool with video-recorded examples for clinical scenarios with treatment plans reviews appearing on first access to the tool and available for revising when needed as part of the formative intervention.

There are no restrictions regarding concomitant care during the trial. This intervention was developed in accordance with the recommendations and the taxonomy proposed by the Cochrane Effective Practice and Organization of Care Group (EPOC). The intervention is described in detail in Fig. 2, following the approach proposed by Perera et al. and the Template for Intervention Description and Replication (TIDieR) (Additional file 3) [38]..

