### Variables

FPs will provide their data before the start of the study. Patient data will be collected by the recruiting FP, who will also be responsible for patient follow-up. All information will be recorded in a case report form designed for the study. Each FP will access the form from their personal computer through the project website using a personal identification code. Four visits were defined for patient data collection: baseline (T0), 6 months (T1), 12 months (T2), and 18 months (T3) (see Table 1).

**Table 1 Tab1:** Visit plan

	T0 (baseline)		T1 (6 m*)	T2 (12 m*)	T3 (18 m*)	Responsible entity
Confirm inclusion/exclusion criteria	X					FP
Written informed consent	X					FP
Sociodemographic variables	X					FP
Morbidity variables and drug treatment plan	X		X	X	X	FP
Randomization of FP´s		X				RU
FP intervention (intervention group)		X				RT
Patient intervention (intervention group)			X	X	X	FP
Mortality				X	X	RT/FP
Hospitalizations				X	X	RT/FP
Functionality (WHODAS), falls, hip fractures			X	X	X	FP
Use of health services			X	X	X	RT
Quality of life	X			X	X	FP
Usability, adhesion, satisfaction			X		X	TG
Costs					X	RT

*T* time, *FP* family physician, *RU* research unit, *IG* intervention group, *RT* research team, *TG* technical group, *m** months from randomization

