
#### Explanatory and adjustment variables

a) Patient variables (first level)
Sociodemographic: age, sex, nationality, region of residence, marital status, socioeconomic status (monthly salary expressed as multiples of minimum wage), family composition (number of people living in the household), indicators of subjective urban vulnerability, based on those collected by the National Health Survey to explore participants’ neighbourhood (noise level, odours, poor-quality drinking water, unclean streets, air pollution, lack of green areas, feral animals and crime), social support (Duke-UNC-11 Questionnaire adapted to Spanish [49]), profession, and social class [50].Morbidity: number and description of chronic diseases based on the International Classification of Diseases in Primary Care (ICPC) as per O’Halloran list [51].Pharmacotherapeutic treatment plan: number and type of drugs prescribed and active ingredient and dose of each drug.

b) FP variables (second level)
Sociodemographic: age and sex.Professional performance: years of professional experience, resident mentor (yes/no), and average workload measured as average daily consultations per FP during the year prior to the start of the study.

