#### Analysis of main effectiveness

The difference in percentages in the composite endpoint of hospital admission or death to 18 months with its corresponding 95% CI. Multilevel analysis will be adjusted considering the combined final variable as the dependent variable; the baseline variables of the patient (first level), the professional (second level), and the intervention group as independent fixed effect variables; and the clustering by physician as a random factor. We will use multiple imputation by chain equations including baseline, 6-month, and 12-month data as available, intervention group, stratification and minimization variables, and other covariates that were informative of missingness. A sensitivity analysis will be conducted to assess whether conclusions may change if assumptions about missing data change.

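### The primary model's first-level covariate list has no measure of current health status, although baseline EQ-5D-5L is collected in both arms before randomisation

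*Protocol article*

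**What the plan says.** The abstract (Statistical analysis) gives the headline result: "The main result is the difference in percentages in the final composite endpoint variable at 18 months, with its corresponding 95% CI". It then adds: "Adjustments by the main confounding and prognostic factors will be performed through a multilevel analysis".

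Analysis of main effectiveness specifies the multilevel model with "the baseline variables of the patient (first level), the professional (second level), and the intervention group as independent fixed effect variables", plus a random effect for physician.

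Explanatory and adjustment variables uses the same first-level label and itemises it in three groups: sociodemographic and social variables (including "indicators of subjective urban vulnerability"), the number and description of chronic diseases, and "Pharmacotherapeutic treatment plan: number and type of drugs prescribed and active ingredient and dose of each drug". EQ-5D-5L, frailty and renal function are not there.

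Table 1 (Variables) has a row for "Quality of life" with entries at T0, T2 and T3, collected by the family physician with no arm restriction. Secondary outcome variables identifies the instrument as EQ-5D-5L. Randomization says physicians are allocated after they have selected their patients and collected the initial data, and that the balance sought is an equal number of physicians per arm.

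Frailty and renal function appear only under Intervention group, where the decision support system uses eCRF data "corrected for patient-specific factors such as sex, renal function, age and frailty".

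**The concern.** The stated aim is to adjust for the main prognostic factors, but the list that defines the first level stops at demographics, diagnoses and drugs. A patient's self-rated health at entry is a natural candidate predictor of later admission or death. Here it is measured before allocation in everyone. WHODAS cannot serve instead, because Table 1 starts it at T1.

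Two things are at stake. The first is some power for the primary comparison, in a trial whose sample size has no slack. The second is protection against chance imbalance: allocation as described balances only the number of physicians per arm, so covariate adjustment is the main safeguard if one arm happens to enrol sicker patients.

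**Working it through.** **1. The plan's own figure.** Inputs from Sample size: 16% versus 10% (a six-point difference), alpha 5% (taken as two-sided), power 80%. With pooled variance and no continuity correction:

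n per arm = [1.960 × √(2 × 0.13 × 0.87) + 0.842 × √(0.16 × 0.84 + 0.10 × 0.90)]² / 0.06² = (0.932 + 0.399)² / 0.0036 = 492

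This gives 984 in total, as stated. Then 984 × 1.08 = 1063, and 1063 × 1.08 = 1148, as stated. After 8% loss, 1148 × 0.92 = 1056 patients are analysed, which is 132 physicians at 8 each. Expected events are 13% of 1056, about 137.

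**2. Power as a function of added prognostic strength.** Effective n per arm = 1056 / DE / 2 / (1 − R²). R² is the share of outcome variance that the added covariate explains beyond those already listed. The documents give no value, so a range is assumed. Two design effects are shown: the printed 1.08, and 1 + (8 − 1) × 0.02 = 1.14, which follows from the stated eight patients per physician.

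| Assumed R² | Power, DE 1.08 | Power, DE 1.14 | Equivalent patients (1148 × R²) |
|---|---|---|---|
| 0 | 79.76% | 77.59% | 0 |
| 1% | 80.15% | 77.99% | 11 |
| 2% | 80.55% | 78.40% | 23 |
| 3% | 80.95% | 78.82% | 34 |
| 5% | 81.75% | 79.65% | 57 |
| 10% | 83.76% | 81.75% | 115 |

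**3. EQ-5D-5L alone, by simulation.** Set-up: 8000 trials per scenario, 132 clusters of 8, ICC 0.02, marginal risks 16% and 10%, logistic regression with cluster-robust standard errors. The comparator model adjusts for age and disease count. The assumed odds ratio for EQ-5D-5L ranges from 1.35 to 1.82 per SD.

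- Weak: 81.1% to 81.7%, a gain of 0.6 points
- Middle: 81.9% to 82.9%, a gain of 1.0 point
- Strong: 81.2% to 83.1%, a gain of 1.9 points

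The Monte Carlo SE of a gain is 0.2 to 0.3 points. The starting levels differ from step 2 because the method and the base model differ, so only the gains should be compared.

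**4. Effect on the risk difference itself.** A second simulation (2000 trials per scenario, 132 × 8) compared the crude risk difference with one standardised from a logistic model containing one baseline covariate. For covariate AUCs of 0.56, 0.61, 0.66 and 0.72, the variance fell by about 0%, 1%, 4% and 8%. The AUC of 0.66 corresponds to a log odds ratio of 0.6 per SD, that is an odds ratio of 1.82, the strong case in step 3. Its 4% variance reduction lies between the 3% and 5% rows of step 2, a gain of about 1.2 to 2.1 points, which agrees with 1.9. A weak covariate gains essentially nothing.

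**5. Chance imbalance.** Suppose baseline EQ-5D-5L has the same clustering as the outcome (assumed). The SD of the between-arm difference in its mean is then √(2 × 1.14 / 528) = 0.066 SD units. To first order, a two-SD imbalance (0.131) shifts the crude risk difference by 0.13 × 0.87 × ln(OR) × 0.131:

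- OR 1.35: 0.1131 × 0.300 × 0.131 = 0.4 points
- OR 1.82: 0.1131 × 0.599 × 0.131 = 0.9 points

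This compares with the six-point target. Any part of such an imbalance that runs through age, diseases or drugs is already covered by the listed variables.

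**The case against.** The strongest reply is that nothing here is an error. The model wording is generic and could admit T0 EQ-5D-5L. The variable section reads partly as a data catalogue, since the dose of every drug can hardly be a model term. Final covariate sets are often left to a separate analysis plan. What weakens this reply is that the section is headed as listing adjustment variables and uses the same first-level label as the model, so the article does define the set, and a reader following it would leave EQ-5D-5L out.

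Three further objections stand. All prognostic strengths are assumed. The simulated comparator is thin (age and disease count), whereas the list also holds disease description, drugs, socioeconomic status and social support, so the true increment is probably smaller. And the headline difference in percentages is stated separately from the model, so adjustment helps it only if a risk difference is derived from that model. The imputation model is already broad, including baseline data as available, so naming EQ-5D-5L there is mostly clarification.

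A reader might infer that frailty and renal function are also in the database for every patient at baseline. The text on clinical data entered at the baseline visit makes this plausible, but both items are mentioned only under Intervention group. They have no row in Table 1 and do not appear in the Control group text, and physicians may update kidney function later. Capture before randomisation in both arms is not established. Requiring these fields at T0 may also come too late: Trial status puts the end of recruitment at about 28 February 2022, before the article appeared.

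A reader might also infer that the neighbourhood items are weak predictors and should give way. The documents say nothing about their prognostic value, so that does not follow.

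**Conclusion.** The point holds in a limited form. The first-level list does not fully deliver the promised adjustment for main prognostic factors, because it omits the one health-status scale that is scheduled for all patients before allocation. The expected benefit is about 0.6 to 1.9 power points for EQ-5D-5L alone, under assumed odds ratios of 1.35 to 1.82 per SD, and close to zero if it adds little to age, diseases and drugs. There is also some protection against a chance imbalance that could move the crude result by roughly 0.4 to 0.9 points in a two-SD case under the same assumptions. This does not threaten the validity of the primary analysis. It is a small improvement worth making because it costs almost nothing.

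**What to change.** - In Explanatory and adjustment variables, add T0 EQ-5D-5L utility to the first-level patient variables.
- In Analysis of main effectiveness, name it as a prespecified covariate of the primary multilevel model and as a variable in the imputation model.
- State that the adjusted risk difference with its 95% CI will be derived from that model (for a logistic model, by standardising over the covariates) and reported alongside the difference in percentages.
- Add frailty and renal function on the same terms only if a check of the eCRF shows that both were recorded before randomisation in both arms. Require no new data collection.
- Leave the neighbourhood items as they are.
- Record the change before outcomes are examined by arm.

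The cost is a few lines of text and one check of the eCRF fields. The downside is one more parameter, set against about 137 expected events, and a few missing baseline values to impute. No patients or visits are added, and the stated sample size is unchanged.

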**Discussion:**

It is important to prevent the cascade of negative health and health care impacts attributable to the multimorbidity-polypharmacy binomial. ICT-enhanced routine clinical practice could improve the prescription process in patient care.

**Trial registration:**

ClinicalTrials.gov NCT04147130. Registered on 22 October 2019

**Supplementary Information:**

The online version contains supplementary material available at 10.1186/s13063-022-06293-x.

## Contributions to the literature

There is lack of evidence about the effectiveness of interventions in primary care to prevent the cascade of negative health care impacts attributable to the multimorbidity-polypharmacy binomial.There are conflicting results on the effectiveness of decision support systems (DSS) to improve medication appropriateness. MULTIPAP-PLUS complex intervention combines a family physician training, a specific type of FP-patient interview, and a DSS to help family physicians.Medical record-implemented DSS could be a tool of great potential, and a co-designed DSS has been adapted to the conditions of clinical practice inside case report forms.

## Background

The progressive ageing of the population leads to an increase in multimorbidity, defined as ≥ 2 concurrent chronic medical conditions or ≥ 3 if a more specific threshold is considered to identify patients with complex health needs [1, 2]. In Spain, the average number of chronic problems in individuals > 75 years of age is 3.2; however, these patients constitute only part of the population with multimorbidity; among so-called older adults (65–74 years), it is 2.8 [3]. The importance of multimorbidity lies in its progressive increase with age [3] and its negative impact on health, reducing the quality of life and functional capacity of those who suffer from it. Likewise, it is associated with an increase in polypharmacy, hospitalizations, surgical complications, and mortality and, consequently, with a greater use of health services and therefore greater costs for health systems [4–7].

Within the framework of multimorbidity, polypharmacy acquires special importance. It is defined as the simultaneous consumption of ≥ 5 drugs and is considered the main determinant of potentially inappropriate prescription (PIP) in the elderly; this term encompasses excessive, incorrect, and insufficient prescriptions [8, 9]. Currently, it is estimated that 40% of the elderly population are polymedicated, having 36.5% of them PIP. This entails an increased risk of drug interactions and adverse drug reactions and therefore a low adherence and underuse of necessary treatments [10]. As people age, their risk of hospitalizations increases, as does their risk of fractures and therefore morbidity [11, 12] and mortality [7, 13]. It is estimated that 35% of elderly polymedicated patients in primary care (PC) develop some adverse effects, with 48.2% of adverse effects related to medication use and 59.1% of these being preventable [14, 15].

To quantify and reduce PIPs in complex patients, various measurement methods have been proposed: explicit, based on the properties of the drugs (BEERS and STOPP/START criteria), and implicit, based on the clinical judgement of the physician, who considers the overall situation of the patient and if the prescription responds to an indication or need, with the Medication Adequacy Index (MAI) being the most accepted method [16–18]. On the other hand, to improve polypharmacy, interventions at various scales have been proposed, for example (a) the professional level (educational programmes for prescribers or consumers); (b) the organizational level (use of electronic medical records, feedback to reduce pharmacological interactions, continuous review of medications, and decision support systems in the care process—DSS); (c) the patient level (education on the use of medications and treatment objectives); and (d) the financial level (prescribed incentives and regulatory interventions) [19].

In recent years, the management of patients with multimorbidity has been studied to provide evidence in the context of European health systems [20]. Spain has implemented the MULTIPAP intervention [21, 22], a complex intervention in the elderly population with multimorbidity and polypharmacy. The MULTIPAP intervention based on the Ariadne principles, which includes international guidelines for the treatment of patients with multimorbidity [21, 23], is effective in improving the appropriateness of medication at 12 months, although we should be cautious in the interpretation of the results given the paucity of evidence for the clinical benefit of the observed change in MAI. The MULTIPAP formative intervention provides clues for approaching this type of patient and identifies areas of improvement in training content. Along these lines, a Cochrane systematic review [24] that evaluates interventions for the management of patients with multimorbidity supports the need to generate more evidence to determine what specific training physicians need in the approach of these patients [25].

In this way, the incorporation of Information and Communication Technologies (ICT) in patient care is an opportunity to introduce medication evaluation tools such as DSS to optimize the care process. The DSS are considered a promising technology that improves medical care and the quality of prescription and reduces prescribing errors. However, more quality studies are needed to establish evidence of its effectiveness and cost-effectiveness in conditions of routine clinical practice [26, 27]. At the European level, some initiatives have been launched that attempt to overcome these limitations [28].

Among the tools available in Spain, CheckTheMeds® [29, 30] is an DSS designed as a health care tool that globally processes demographic, clinical and pharmacological data to detect issues related to medications (underdosing, overdosing, duplicates, therapeutic inertia, allergy alerts, drug-drug and drug-disease interactions, including inappropriate drug criteria, etc.). Its recommendations are based on the best available evidence. This tool has already been incorporated into some hospital pharmacy and PC services to generate treatment review reports that are subsequently sent to doctors. In our group within the MULTIPAP intervention, we tested the tool, offering proposals for improving and establishing a framework of collaboration with the platform that allows the use of its full potential for research studies in the field of PC [31, 32]. After the experience with the MULTIPAP project, the MULTIPAP Plus intervention was developed, introducing organizational measures that family physicians (FPs) have identified as essential. These include the inclusion of a DSS in the care process and its link with clinically relevant processes for patients, as well as the study of the economic costs involved in these clinical processes in the health system.

Although DSS may reduce PIPs, interventions in PC focused on patients with multimorbidity and polypharmacy with patient-relevant outcomes as hospital admission, mortality and quality of life between others are a priority, and several systematic reviews agree on the importance of implementing well-designed RCTs that incorporate outcome variables of clinical relevance for the patient, as well as the socioeconomic impact [24, 33].

